#### Randomisation

Randomisation will occur after baseline assessments. Families will be randomly allocated to treatment or ETAU conditions in a 1:1 ratio. A computer-generated randomisation sequence will be created by an independent statistician external to the study location using Research Randomizer (randomizer.org). Complete, temporal participant lists will be provided to the independent statistician, who will match them to the randomisation sequence and return allocations for implementation.

#### Masking

All investigators and research assistants will be masked to the allocations of families. Due to the nature of the intervention, complete masking of participants and implementation staff is not possible. Staff will receive training on maintaining masking protocols during data collection, research and implementation teams will operate separately, and participants will be instructed not to reveal their allocation. Research assistants will document instances where allocation is accidentally revealed. The level of (un)masking of the research assistants will be assessed at the end of each follow-up interview by asking research assistants if allocation was explicitly revealed during the interview. These data will be used to assess the integrity of masking and to control for possible bias in impact analyses, in addition to being reported as a study limitation.

### Outcomes

Outcome measures were selected based on prior validation with similar populations in Arabic. During the feasibility study, measures underwent a multi-step translation process (*i.e.*, forward and backtranslations by independent bilingual team members, translation workshops and cognitive interviewing) and psychometric evaluation to ensure validity and relevance for the target population (Brown et al., 2024). The instruments can be found in Table 3.

**Table 3. tab3:** Key effectiveness and implementation measures

Construct	Measure	Scale construction	Contextual validity
** *Primary upstream outcomes* **			
Family functioning (adolescent-report)	Adapted Systemic Clinical Outcome and Routine Evaluation–15 (SCORE–15) (Stratton et al., 2010)	16-item measure (15 + 1 added) (range: 16–80) 5-point Likert scale rating applicability to family Covers strengths and adaptability, feeling overwhelmed by difficulties and communication quality Lower score indicates better functioning	Very good internal consistency (⍺ = 0.90) in feasibility study (Brown et al., 2024); good psychometric properties with similar populations (Hamilton et al., 2015)
Parenting practices (caregiver-report)	Arabic Dimension of Parenting Scale (Miller et al., 2020)	25-item measure (24 + 1 added) (range: 25–75) 3-point Likert scale (rarely, sometimes, often) Assesses parental warmth and responsiveness, positive parenting, and harsh discipline practices Higher scores indicate more positive parenting	Very good internal consistency in feasibility study (⍺ = 0.88) and in trial with psychometric testing of Arabic version used with Syrian refugees (⍺ = 0.87) (Miller et al., 2020)
Caregiver mental health (caregiver-report)	Kessler–10 (K10) (Kessler et al., 2003, 10)	10-item brief screening scale (range: 10–50) 5-point Likert scale Higher scores indicate more distress	Good internal consistency (⍺ = 0.85) in the feasibility study
** *Primary downstream outcome* **			
Adolescent emotional and behavioural difficulties (adolescent-report)	Strengths and Difficulties Questionnaire (SDQ) (Alyahri and Goodman, 2006)	25-item measure (range: 0–40) 3-point frequency scale (not true, somewhat true, certainly true) Covers emotional problems, conduct problems, hyperactivity, peer problems and prosocial behaviours Higher scores indicate greater difficulty	Good internal consistency (⍺ = 0.73–85) and psychometric testing of both child- and adult-report Arabic versions with similar populations (Ababneh and Alomari, 2016; Emam et al., 2016; Atoum et al., 2018; Al-Hendawi, 2023)
** *Caregiver-reported secondary outcomes* **			
Family functioning (caregiver-report)	Adapted Systemic Clinical Outcome and Routine Evaluation–15 (SCORE–15)	Same as adolescent-report (above)	Very good internal consistency (⍺ = 0.89) in feasibility study
Financial literacy and capability (caregiver-report)	Financial knowledge, behaviours, decision-making skills and well-being	Measure developed for the present study	Similar measures of financial literacy, capability and well-being have been used with populations in Jordan (Alqam and Hamshari, 2024)
Emotional regulation (caregiver-report)	Adapted Difficulties in Emotion Regulation Scale 18 (DERS–18) (Victor and Klonsky, 2016)	19-item measure (18 + 1 added) (range: 19–95) 5-point Likert scale assessing frequency (1 = almost never; 5 = almost always) Assesses emotional awareness, acceptance, goal-directed behaviour and regulation strategies Higher scores indicate more difficulties	Very good internal consistency (⍺ = 0.87) in feasibility study
Mental well-being (caregiver- and adolescent-report)	Warwick-Edinburgh Mental Wellbeing Scale (WEMWBS) (Stewart-Brown and Janmohamed, 2008)	14-item measure (range: 14–70) Items rated on a 5-point scale Assesses positive mental health and well-being	Acceptable internal consistency (⍺ = 0.72) in trial with Syrian refugees (Miller et al., 2020)
Adolescent emotional and behavioural difficulties (caregiver-report)	Proxy-reported SDQ (Goodman, 2001)	25-item measure (range: 0–40) 3-point frequency scale (not true, somewhat true, certainly true) Covers emotional problems, conduct problems, hyperactivity, peer problems and prosocial behaviours Higher scores indicate greater difficulty	Acceptable internal consistency (⍺ = 0.73) and psychometric testing of parent- and teacher-report Arabic versions with Arabic-speaking adolescent populations (Ababneh and Alomari, 2016; Emam et al., 2016; Al-Hendawi, 2023)
Adolescent self-perception and belief in personal goal attainment (adolescent-report)	Children’s Hope Scale (Snyder et al., 1997)	6-item continuous measure (range: 0–3) averaging the total responses 3-point Likert scale rating how often they think/feel each item, ‘Almost never’ to ‘Most of the time’ Higher score suggesting higher perceived hope	Very good internal consistency (⍺ = 0.93) in Jordan (O’Leary et al., 2015); good psychometric properties with forcibly displaced adolescent populations in South Sudan (Blackwell et al., 2023), Uganda (Metzler et al., 2022), Burundi, Indonesia and Nepal (Haroz et al., 2017)
** *Implementation and process evaluation measures* **			
Proactive family-level case detection	ReachNow family version	Illustrated vignettes showing a prototype family experiencing multiple psychosocial and financial challenges Simple decision algorithm to identify families in need of mental health care Used by community outreach staff for family identification	Approximately 70% of children identified using the tool were confirmed in need of mental healthcare in clinical assessment in Sri Lanka and Palestine (van den Broek et al., 2021, 2023); an adapted tool was piloted with 78 families in Jordan during feasibility study
Facilitator competency	Family Act Tool (FamilyACT) (WHO, 2025)	Observational rating tool for MHPSS interventions delivered by non-specialists Developed for the World Health Organization EQUIP (Ensuring Quality in Psychological support initiative) platform Adequate single-rater reliability (ICC: 0.40) Sensitivity to change over time (Wilcoxon signed-rank tests, *α* < 0.05)	Developed for interventions where non-specialists deliver MHPSS interventions (Kohrt et al., 2025); with similar tools used in previous studies with high inter-rater reliability (ICC: 0.71–0.89) (Pedersen et al., 2021; Mwenge et al., 2022), single-rater reliability (ICC: 0.41–0.75) and demonstrated sensitivity to change (Jordans et al., 2021)
Implementation fidelity	Module completion, supervisor observation and programme monitoring and supervision records	Programme monitoring Documentation of supervisor observations Debrief meetings on facilitator module completion and implementation Fidelity will be calculated as the percentage of core components delivered as intended following session observations by the supervisor	NA
Implementation acceptability and potential for scale	Module attendance, acceptability and barriers and facilitators to implementation	Documentation of module completion and session participation per family member, with reasons for non-attendance recorded Qualitative focus groups and interviews	NA
Process documentation	Programme monitoring and debrief notes	Programme monitoring Debrief meetings on progress and challenges with outreach, family module completion and implementation	NA

**Table 4. tab4:** Process evaluation outcomes and measures for implementation, effectiveness and potential sustainability by the RE-AIM framework

Dimension	Study definition	Participant level	Organisation level
Reach	Representativeness of the participants who enrol and the individuals’ willingness to participate in the study	Qualitative: Reasons for non-participation or discontinuation Monitoring: Attendance records	Debrief meetings: Barriers to recruitment Quantitative: ReachNow evaluation
Effectiveness	Impact of the intervention on target outcomes, including potential negative effects, heterogeneity of effects and mechanisms of change	Quantitative: Intervention effectiveness; Subgroup analyses; Moderation and exploratory mediation analyses Qualitative: Perceived impact and pathways of change	Monitoring and debrief meetings: Adverse events monitoring Qualitative: Perceived impact and pathways of change
Adoption	Organisational support to deliver the intervention, including acceptance of the intervention among implementing organisations and reasons for (non-)adoption	Quantitative: Moderation of intervention effects by facilitator characteristics	Quantitative: Facilitator competency (FamilyACT) Qualitative: Perceived feasibility, acceptability and sustainability of the intervention
Implementation	Completion of intervention components as intended, as well as acceptability (participants’ use of the intervention) and potential for scale-up	Qualitative: Acceptability of core and optional modules	Monitoring: Completion of modules Qualitative: Barriers and facilitators to implementation; Recommendations for sustainment and scale
Maintenance	The extent to which a behaviour is sustained and the intervention becomes institutionalised	Not applicable to this study	

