### Intervention and control conditions

#### Whole-family intervention: StrongerTogether

Intervention characteristics are reported in accordance with the template for intervention description and replication (TIDieR) checklist (Hoffmann et al., 2014). StrongerTogether is a modular, whole-family intervention addressing multiple interconnected family challenges simultaneously. It is positioned as a Level 3 intervention on the IASC MHPSS pyramid,^1^ providing focused, non-specialised mental health support for individual families with psychological distress (IASC, 2007). Non-specialised services rely on task-sharing, an evidence-based approach involving the delivery of mental health services by trained providers who do not have specialised or formal mental health training, improving accessibility (Kazdin, 2019; Raviola et al., 2019).

For each family, the intervention is delivered to at least one caregiver and all adolescents aged between 10 and 17 years. It comprises seven core sessions (including six content-specific sessions and a collaborative ‘transition’ session) addressing family roles, communication, problem-solving and future planning, followed by four optional modules of up to four sessions each covering parenting, caregiver mental health, disagreements and financial literacy, as needed. Session content is manualized, a detailed overview of which can be found in Table 1. Sessions take place weekly at a community centre and are delivered by one non-specialist facilitator face-to-face with individual families, with the support of an assistant to coordinate logistics and provide activities for younger children who may attend but not engage in the entire session. Each session involves a 90-min guided activity or discussion with the entire family, followed by a 30-min discussion with caregivers alone to consolidate the information and support them in their role to implement the strategies. To facilitate home practice and sharing of content with non-attending family members, session content is summarised and provided to families through simple, illustrated handouts and audio-recordings created by the StrongerTogether master trainer to accommodate varying literacy levels.

**Table 1. tab1:** Module content and aims

Central family intervention module		Number of sessions
Module	Aims	

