#### Enhanced treatment as usual (ETAU)

The control condition will be an ETAU consisting of one 30–45 min session comprising a structured, family psychoeducation session delivered by a non-specialist facilitator to the participating caregivers and index adolescent. The scripted session consists of (1) sharing the screening results with the family; (2) discussing common and simple self-care strategies to manage distress; and (3) providing information about available MHPSS, caregiving and financial literacy resources and services. The ETAU will be delivered by non-specialist facilitators, who are different from the StrongerTogether facilitators and who receive a separate 1-day training on the delivery of the psychoeducation session.

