##### Data collection

Research assistants will collect survey data from at least one caregiver and the index adolescent at baseline (T0: no more than 3 weeks before intervention), midline (T1: post-core modules), endline (T2: post-optional modules, within 3 weeks of the final session) and 6-month follow-up (T3). Surveys will collect sociodemographic information, outcome measures and hypothesised mediators (see below). After baseline, intervention families will be contacted to schedule sessions. Families discontinuing the intervention will be encouraged to complete the remaining assessments.

Research assistants will collect qualitative data using semi-structured guides after endline from a purposive subsample (*n* = 15) to examine implementation, effectiveness and potential sustainability. At least 10 families who completed the intervention and five who dropped out will be selected for interviews, ensuring representation across family composition, attendance and change in outcomes at T1 and T2. Focus group discussions (*n* = 4) and key informant interviews (*n* = 8) will be conducted with stakeholders from implementing organisations, including facilitators, supervisors and other staff, to explore implementation factors, programme sustainability and recommendations.

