### Trial and adverse events monitoring

A trial management committee will monitor the implementation of study procedures and protocol deviations. All research staff will follow War Child’s Child Safeguarding Policies and will record any suspected maltreatment, exploitation or other violations and report these cases and other adverse events within 24 hours for review and appropriate action. To manage participant distress, multiple mitigation measures will be in place: (1) research assistants will be trained to recognise signs of distress and remind participants they can skip questions or withdraw at any time during all assessments; (2) referral pathways have been established for families requiring support beyond the scope of the intervention, including those who experience distress during intervention sessions or where severe mental health or protection concerns become apparent; (3) all staff have been trained to refer cases in accordance with safeguarding policies. A Data Safety Management Committee will also be established and mandated to provide oversight on adverse events and safety protocols for the trial.

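### Adverse-event detection as described is unequal by arm; asking the same risk questions in both arms at T1, T2 and T3 would be a cheap improvement

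*Protocol article*

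**What the plan says.** Table 4 defines the Effectiveness dimension as "Impact of the intervention on target outcomes, including potential negative effects, heterogeneity of effects and mechanisms of change". In the organisation-level column of that row, the source for adverse events is "Monitoring and debrief meetings: Adverse events monitoring". Table 3, under process documentation, describes the debriefs as "Debrief meetings on progress and challenges with outreach, family module completion and implementation".

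Contact with programme staff differs by arm. For StrongerTogether, "It comprises seven core sessions", followed by four optional modules of at most four sessions each. "Sessions take place weekly at a community centre", and each lasts 90 minutes with the family plus 30 minutes with the caregivers. The facilitators' weekly group supervision covers the management of adverse events. On the other side, "The control condition will be an ETAU consisting of one 30–45 min session", and no comparable supervision is described for the ETAU facilitators.

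One channel is common to both arms. Under Trial and adverse events monitoring, research staff must record suspected maltreatment and other violations and "report these cases and other adverse events within 24 hours for review and appropriate action". The Discussion adds that research assistants are trained to report observations and disclosures of severe concerns at every round of data collection. Structured questions on suicidality, substance abuse, psychosis and family violence appear in the screening protocol (Table 2, criterion 2). For the T0 to T3 surveys, the Data collection section says: "Surveys will collect sociodemographic information, outcome measures and hypothesised mediators".

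**The concern.** A harm can be counted only if someone notices it. Intervention families meet a facilitator week after week, and that facilitator's supervisor asks about adverse events. ETAU families meet a facilitator once. If events from these channels are set side by side by arm, a harmless intervention would tend to look more harmful than ETAU because it is watched more closely. Conversely, a true excess of harm could be put down to extra contact. That ambiguity matters here because the programme brings distressed families together and works on disagreements, and because the oversight committee is charged with adverse events.

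The research visits could balance this, but as described they pick up serious risks passively. None of the outcome measures in Table 3 is described as covering suicidality, partner violence or coercion, which Table 2 treats as serious at entry.

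**Working it through.** The article gives no adverse-event rate, detection probability or between-arm harms test, so there is no figure of its own to reproduce. What can be checked is the number of contacts and what that implies under stated assumptions.

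**Contacts, from the article**
- Intervention sessions: 7 core + 0 to 4 × 4 = 16 optional, so 7 to 23.
- Intervention time: 7 × 120 = 840 min to 23 × 120 = 2,760 min, that is 14 to 46 h.
- ETAU: 1 session, 30 to 45 min.
- Ratio of time: 840/45 ≈ 19 to 2,760/30 = 92.
- Post-randomisation research visits common to both arms: T1, T2, T3 = 3.
- Total contacts: ETAU 1 + 3 = 4; intervention 7 + 3 = 10 to 23 + 3 = 26.

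**Illustrative model.** Assume equal true event rates and the same chance q of noticing an event at each contact, independently. The share detected is 1 − (1 − q)^k with k contacts. The values of q are assumptions.

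| q | ETAU, k = 4 | Intervention, k = 10 | Intervention, k = 26 | Ratio to ETAU |
|---|---|---|---|---|
| 0.05 | 18.5% | 40.1% | 73.6% | 2.2–4.0 |
| 0.10 | 34.4% | 65.1% | 93.5% | 1.9–2.7 |
| 0.20 | 59.0% | 89.3% | 99.7% | 1.5–1.7 |
| 0.30 | 76.0% | 97.2% | 100% | 1.3 |
| 0.50 | 93.8% | 99.9% | 100% | 1.07 |

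For any q strictly between 0 and 1 the ratio exceeds 1, because the intervention arm has more contacts. Its size is not fixed by anything in the article.

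**Threshold for missing more than half of ETAU events.** Solve (1 − q)^4 = 0.5: q = 1 − 0.5^(1/4) = 0.159. Above that value, most ETAU events are detected in this model.

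**If counts were tested.** With an assumed true rate of 10% in both arms and 550/2 = 275 families per arm, the chance of p < 0.05 is 0.32 to 0.87 at q = 0.05 and 0.14 to 0.17 at q = 0.30, against a nominal 0.05.

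**After the fix.** If only answers to the same questions at T1, T2 and T3 are compared, k is 3 in each arm and the modelled ratio is 1.0 for any q. This assumes equal retention and equal willingness to disclose.

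**The case against.** The case against is substantial, and several stronger readings fall to it.

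- **A reader might infer that a planned harms comparison is biased.** The article describes no between-arm test, rate or table of adverse events. It describes recording, rapid reporting, referral and committee oversight. The problem arises only if counts are compared. Even so, Table 4 places negative effects within the impact of the intervention, which in a two-arm trial invites comparison with control.
- **A reader might infer that most ETAU events will be missed.** That needs q below about 0.16, a figure the documents do not supply.
- **A reader might infer that deterioration in ETAU families goes unseen.** It does not. The participant-level cell of the same Table 4 row lists the quantitative effectiveness analyses, and distress, family functioning and harsh discipline are measured alike in both arms. The uncovered area is narrower.
- **A reader might infer that the 24-hour duty leaves facilitators out.** It is written for research staff, but the same section says that all staff are trained to refer cases. This is largely a matter of wording.
- **The model is crude.** It lets a contact detect an event that has not yet happened, gives every kind of contact the same q, and reaches 23 sessions only if a family takes all four optional modules at full length. Its ratios show direction and possible range, not a forecast.
- **This is a condensed article.** Event forms and schedules may stand in the full protocol. The point therefore rests on the source that Table 4 does name and on the contact pattern the article sets out, not on missing detail.

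What stands is that the opportunity for detection is unequal and the common channel, as described, is passive. That channel reduces the imbalance without removing it.

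**Conclusion.** The point holds as an inexpensive improvement. As described, adverse-event detection favours the intervention arm: 10 to 26 post-randomisation contacts against 4, with adverse-event supervision described only for StrongerTogether facilitators and structured risk questions described only at screening. The gap concerns events outside the outcome scales, such as suicidality, partner violence and coercion. Raw counts would tend to be higher in the intervention arm even with equal true rates. The illustrative ratio is about 1.1 to 4.0 for assumed q of 0.50 to 0.05, and rests on equal true rates, a common q and independent contacts. The direction follows from the contact counts if sessions have any chance of revealing an event; the size is unknown.

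**What to change.** At the existing T1, T2 and T3 visits, have the masked research assistants put the existing structured risk questions to caregivers in both arms, with one added question on new harm since the last visit. Ask them after the outcome measures, so that they cannot influence those answers.

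Base any between-arm statement on harms, and any by-arm table for the oversight committee, on events found this way. Continue to record and act on events found through sessions, supervision or debriefs, but list them separately, with a field for source of detection. Revise the source in the Effectiveness row of Table 4 to match.

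Putting the same questions to the index adolescent is optional and should go through safeguarding review first, because the screening questions are described as administered to caregivers.

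The cost is a few minutes per visit, one field on the event form, revised wording in Table 4, and somewhat more referrals. No extra visits or staff are needed.
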